#### Inclusion Criteria

Eligible participants are adult, aged ≥18 years, patients with T2D diagnosed within the last 5 years, Swedish-speaking, noninsulin-treated at inclusion, and own a smartphone. They will be randomized to either an intervention group (n=46) or a control group (n=46). An external comparison group (n=46) will be recruited from 2 different HCCs to analyze for a possible Hawthorne effect. The recruitment process will start in September 2018. The study flow chart is presented in Figure 1.

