**Methods:**

This study is a 12-month, 3-armed, nonblinded randomized controlled trial (RCT), which will be conducted in 6 primary health care centers (HCCs) in northern Sweden. Eligible participants will be randomized to either an intervention group (n=46), a control group (n=46), or an external group (n=46) for comparison. The intervention group will receive the mobile app, and the control group will receive a minimal intervention (diabetes brochure) and the usual standard of care. Changes in glycated hemoglobin (HbA_1c_) will be the primary outcome measure.

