The purpose of the interactive self-management support (iSMS) project is to include digital tools by offering the use of a smartphone or tablet app to support people living with T2D in self-management and to facilitate interaction with DSNs. This study protocol outlines a randomized controlled trial (RCT) to evaluate the effectiveness of person-centered iSMS in primary health care. This study puts a particular focus on how digital technology is used as a tool for self-management in daily life, wherein patients with T2D manage their illness in closer collaboration with DSNs through self-monitoring and self-care activities. The objectives of this project are to develop and evaluate a person-centered iSMS intervention in primary health care for people with T2D in addition to their usual diabetes care. The hypotheses are that an iSMS program will decrease glycated hemoglobin (HbA_1c_) and improve metabolic measurements, such as BP (mm HG), body mass index, waist circumference (cm), and total and high-density lipoprotein cholesterol (mmol/L). Furthermore, we hypothesize that an iSMS program will improve lifestyle habits such as physical activity, diet, and smoking; decrease the need for SMS and changes in medical treatment; increase diabetes empowerment; increase diabetes-dependent quality of life (QoL); improve illness perception; and improve eHealth literacy in the intervention group compared with an internal (intervention and control) and external control group at 4 and 12 months’ follow-up.

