#### Exclusion Criteria

The exclusion criteria are planned (within 2 years) or current pregnancy, life-threatening physical illness (eg, cancer), and cognitive impairment. Furthermore, patients not responsible for their care and those not residing in their home environment (eg, those in nursing homes and in-patient hospital wards) will be excluded. The recruitment process will build on patients identified in the electronic medical record system at each HCC cared for by DSNs. Participants will be contacted via phone by the research team to discuss the study and gain informed consent about the randomization process. Informed consent will be obtained from all participants before they are enrolled in the study.

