#### Control Groups

The control groups will be included in the data collection of laboratory values as well as questionnaires, similar to the intervention group. In addition to this, they will receive the usual care and take part in a minimal intervention in the form of a brochure about self-management of diabetes.

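### The external group is recruited to examine a Hawthorne effect but, as most naturally read, is studied as closely as the internal controls, so the contrast cannot isolate such an effect

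*Protocol article*

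**What the plan says.** The Inclusion Criteria section gives one reason for recruiting the third group: "An external comparison group (n=46) will be recruited from 2 different HCCs to analyze for a possible Hawthorne effect".

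The Control Groups section, in the plural, sets out what such groups undergo: "The control groups will be included in the data collection of laboratory values as well as questionnaires, similar to the intervention group". It adds that "they will receive the usual care and take part in a minimal intervention in the form of a brochure about self-management of diabetes". It draws no line between internal and external controls.

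The hypotheses in Background compare the intervention group at 4 and 12 months with an "internal (intervention and control) and external control group", so the external group is called a control group there. Under Exclusion Criteria, consent is universal: "Informed consent will be obtained from all participants before they are enrolled in the study".

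The Abstract (Methods) is less clear. It says "the control group will receive a minimal intervention (diabetes brochure) and the usual standard of care", in the singular, and lists the third group separately: "or an external group (n=46) for comparison". It does not say what that group receives.

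**The concern.** To separate an observation effect from everything else, at least two groups must differ in how much they are observed and be alike in other respects. The sections above appear to arrange the opposite. The two control groups are observed alike but differ in health care center (HCC), in exposure to nurses trained in the intervention, and in whether participants know they were allocated away from the app.

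At stake is a stated aim of the trial. A small internal-versus-external difference invites the statement that there was no Hawthorne effect, and a large one invites the reverse. The design would support neither. An analysis plan could not repair this, because the limit lies in who is observed and how, not in the choice of model.

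**Working it through.** The plan gives no figure for this contrast. Its sample-size statement concerns intervention versus control and does not bear on the point. The check is therefore mainly a comparison of sections.

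**Step 1: which groups are the control groups?** There are three groups: intervention, control and external. Background names the external one as a control group. Only two groups can be meant by the plural in the Control Groups section, so it most naturally covers both.

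**Step 2: what do the groups share?**

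| Feature | Internal control | External | Source |
|---|---|---|---|
| Informed consent | yes | yes | Exclusion Criteria |
| Laboratory values and questionnaires | yes | yes, by the plural | Control Groups |
| Usual care plus brochure | yes | yes, by the plural | Control Groups |
| HCC | intervention HCCs | 2 different HCCs | Inclusion Criteria |
| Nurses trained in app and needs assessment | yes | not stated; presumed no | Intervention; Diabetes Specialist Nurses |
| Aware of not being allocated the app | yes | no such allocation described | Randomization and Blinding |

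**Step 3: the contrast.** Write the expected HbA1c change as a sum: U (usual care), H (being studied), B (brochure), K (contamination), A (reaction to allocation) and C (centre).

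- Internal control: U + H + B + K + A + C_int
- External: U + H + B + C_ext
- Difference: (H - H) + (B - B) + K + A + (C_int - C_ext) = K + A + (C_int - C_ext)

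H drops out whatever its size. If K, A and the centre difference were all zero, a two-sided 5% test would reject 5% of the time for H = 0, 2, 4 or 6 mmol/mol alike. Intervention versus external does not help, because the intervention group is observed in the same way.

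**Step 4: how large could the centre term be?** This illustration uses the plan's SD of 9 mmol/mol. The intraclass correlation (ICC, 0.02 to 0.05) and the number of internal HCCs (6 or 4) are assumptions. The 95% half-width from centre variation alone is 1.96 × 9 × √ICC × √(1/2 + 1/k):

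- ICC 0.02, k = 6: 17.64 × 0.1414 × 0.8165 = 2.0 mmol/mol
- ICC 0.05, k = 4: 17.64 × 0.2236 × 0.8660 = 3.4 mmol/mol

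The plan's design difference between intervention and control is 6 mmol/mol.

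**Step 5: what would an unobserved external group give?** With B the same in both groups, the difference would contain H. At 46 per group and SD 9, ignoring clustering, SE = 9 × √(2/46) = 1.88. The smallest difference detectable with 80% power is 1.88 × (1.960 + 0.842) = 5.3 mmol/mol. Power would be about 19%, 57% and 89% for assumed H of 2, 4 and 6 mmol/mol. K, A and the centre difference would still be mixed in, and participants who have consented still know they are in a study.

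**The case against.** The strongest objection is that the shared data collection and brochure are inferred, not stated. The Abstract uses the singular and is silent on the external group, the article uses the plural loosely elsewhere (Randomization and Blinding speaks of control groups in a 1:1 ratio with the intervention), and the flow diagram that might settle it is not available here. This stands as a caveat. The plural read with Background is still the more natural reading, and no section says the external group is observed less. If that was the intention, the sections need reconciling anyway.

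Second, the article does not define the effect it means. A reaction of staff or of a whole centre to taking part could show up between internal and external controls. That also stands, and it is why the point is limited to a participant-level response. A centre-level reaction is not described, and it would be inseparable from ordinary centre differences.

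Third, the article is condensed, and procedures for a secondary group may be in a fuller document. But the point rests on what the article does state: a purpose and a procedure that do not fit together.

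A reader might go further and infer that a third of the participants serve no purpose. The documents do not support that: the Abstract and the Background hypotheses also use the group as a comparator. Nor do they support saying that any Hawthorne conclusion would be false. No rule for interpreting the contrast is given, and such a conclusion would be unsupported rather than shown to be wrong.

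**Conclusion.** The point holds in limited form and should be acted on. On the most natural reading, the internal-versus-external contrast carries no information about a participant-level response to being studied: the expected contribution of such a response is zero whatever its true size. This assumes that the Control Groups section covers the external group and that the observation effect is additive and equal in both groups. The contrast reflects contamination, reaction to allocation and centre differences.

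The group affected is 46 of 3 × 46 = 138 participants, one third, with respect to the one reason given for recruiting it. The 2.0 to 3.4 mmol/mol range for centre variation is only an illustration under assumed ICCs, and the conclusion does not depend on it. The randomized comparison of intervention with internal control is unaffected.

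**What to change.** In Inclusion Criteria, restate the purpose of the external group as a non-randomized comparison, recruited from 2 different HCCs, to explore contamination of usual care at the intervention HCCs. Acknowledge that it is confounded with centre, and drop the Hawthorne inference. State whether nurses at the external HCCs receive the training, since the contamination reading depends on it. Bring the Abstract, which lists the external group among the randomized options, into line. This costs wording only, and the comparator role in the Abstract and Background stays.

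If the external group was meant to be observed less, reconcile the Abstract, Inclusion Criteria and Control Groups sections to say so. One form is HbA1c from patient records only, which Primary Outcomes already names as the source, with brochure provision the same as for the internal controls. Withholding the brochure as well would mix a brochure effect with the observation effect. This option gives up the questionnaire comparisons with the external group, including those among the Background hypotheses. It also leaves centre confounding in place, so any Hawthorne statement would remain exploratory.

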**Figure 1 figure1:**
[figure not shown]
Flow diagram of trial design.

#### Exclusion Criteria

The exclusion criteria are planned (within 2 years) or current pregnancy, life-threatening physical illness (eg, cancer), and cognitive impairment. Furthermore, patients not responsible for their care and those not residing in their home environment (eg, those in nursing homes and in-patient hospital wards) will be excluded. The recruitment process will build on patients identified in the electronic medical record system at each HCC cared for by DSNs. Participants will be contacted via phone by the research team to discuss the study and gain informed consent about the randomization process. Informed consent will be obtained from all participants before they are enrolled in the study.

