#### Co-Designed Workshop

Several activities to prepare for the co-design and participatory workshop have been completed. Individual interviews among persons with T2D treated in Swedish primary health care centers (HCCs) were conducted to gain an understanding of their perceptions about and experiences of using eHealth services for self-management [19]. Furthermore, focus group interviews have been conducted with primary health care nurses about their perceptions of working with digital resources and iSMS in the care of people with chronic conditions, including T2D [20]. These earlier studies have been the basis for the development of the intervention.

A multistakeholder workshop was held on 16 September, 2016, which 27 invited participants attended, (5 were academic representatives, 6 were living with T2D, 2 were relatives of persons living with T2D, and 1 was a medical doctor and also the head of primary health care in the County Council). Furthermore, 10 were DSNs, 1 worked with information technology development in the County Council health care service and lastly, 2 were representatives of a Swedish company that develops apps for people living with diabetes.

The purpose of the workshop was to involve various participants in ideas about the design of the app, thereby influencing and developing the intervention and choice of app. During the workshop, the potentials and limitations of SMS with digital technology were explored and how SMS could be designed to motivate self-management in everyday life, at work and in the patients’ daily life with diabetes, was considered. The workshop used both focus group discussions with mixed groups of representatives and mentometers to answer questions. During the workshop, it was revealed that the most important needs were related to person-centeredness, accessibility, and effectiveness. The summary of the results from the workshop suggested guidelines for setting up the intervention (manuscript, [name] et al, 2018, unpublished data) and provided guidance in planning the 1-year intervention, expected to start in autumn, 2018.

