#### Diabetes Management App

The diabetes management app, mySugr, offers data tracking and coaching services for people living with type 1 or type 2 diabetes. The mySugr App is a registered certified medical device, and carries the CE marking (Medical Devices Directive 93/42/EEC). Furthermore, the app is registered with the Food and Drug Administration, and per se, it is required to meet the highest of data security and reliability standards. The app is available for iOS and Android operating systems for mobile access. There is easy manual input of data, which may be synchronized with selected glucose meters via Bluetooth, and one can easily log in and maintain a record of diabetes clinical data. The app uses these data to provide analysis and trending results. Currently, the app offers features for self-monitoring of diet, exercise, blood sugar, smoking, weight, and medication as well as gamification to support improved self-management. Reminders and self-reflection are linked to these areas, as are statistics and visualization [31-33].

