### Power Calculation and Sample Size

A power calculation showed that with a sample of 46 participants per group, a power of 80% with an alpha<.05 will demonstrate significant HbA_1c_ difference of 6 mmol/mol between the groups and a within-group SD assumed to be 9 [10]. This means that there is an 80% likelihood that the study will yield a statistically significant effect and allow us to conclude that the mean HbA_1c_ differs between the intervention group versus the control group. To compensate for dropouts, the study needs to enroll 46 participants per group for a total of at least 120 participants.

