### Randomization and Blinding

Eligible participants will be randomized to either the intervention or the control groups in a 1:1 ratio. Owing to the nature of the intervention, participants will be aware of their treatment allocation. Therefore, the blinding of participants will not be possible. However, DSNs in charge at HCCs will not be involved in the randomization, preparation of the envelopes with study information, or statistical analyses.

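### The eligibility rules admit people who already use the study app, and no listed item records app use, so the HbA1c contrast may be diluted by an unknown amount

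*Protocol article*

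**What the plan says.** **The app.** The Diabetes Management App section describes an existing certified product for people with type 1 or type 2 diabetes: "The app is available for iOS and Android operating systems for mobile access".

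**Who may enter.** The Inclusion Criteria ask for adults with type 2 diabetes diagnosed in the last five years who speak Swedish and are "noninsulin-treated at inclusion, and own a smartphone". This applies to controls as well as to the intervention group.

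**Who may not.** "The exclusion criteria are planned (within 2 years) or current pregnancy, life-threatening physical illness (eg, cancer), and cognitive impairment". The same section then adds people who are not responsible for their own care and people not living at home. Neither list mentions current use of the study app.

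**What is recorded.** Outcome Assessments lists demographics, questionnaires, laboratory and physical measures, diabetes duration, tobacco, medication, diet and exercise. Use of a diabetes app is not on the list at baseline, 4 months or 12 months. The Intervention section mentions system logs of messages and glucose values, but nothing comparable for controls.

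**What the arms receive.** The intervention group gets SMASc scoring, a tailored plan, nurse interaction, the app and a website. The control groups get usual care and a brochure.

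**The concern.** The app is a central part of what separates the arms, and it is not study-only software. Requiring a smartphone selects people who are able to run it already. A centre applying the published criteria would randomise a current user. If allocated to control, that person already has one main component of the intervention. If allocated to the intervention, that person gains less than a new user would.

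In either arm such people carry less treatment contrast, so the average HbA1c difference shrinks. Randomisation balances their number on average but does not restore the lost contrast, and no analysis can recover it afterwards. With app use unrecorded, a null result could not be separated into an intervention that does not work and a control group that partly had it.

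**Working it through.** **Inputs from Power Calculation and Sample Size.** The plan works "with a sample of 46 participants per group, a power of 80% with an alpha<.05", for a "difference of 6 mmol/mol between the groups and a within-group SD assumed to be 9". Allocation is 1:1 between intervention and control (Randomization and Blinding). The article does not state whether the test is one- or two-sided, so two-sided 0.05 is assumed.

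**Step 1: the plan's own figure.**
- n per group = 2 × (SD/δ)² × (1.960 + 0.842)² = 2 × (9/6)² × 7.85 = 35.3, so 36 per group. A t-test calculation gives 36.3, so 37.
- With 46 per group, SE = 9 × √(2/46) = 1.877 and power = Φ(6/1.877 − 1.960) = Φ(1.237) = 89.2% (t-test 88.6%).
- So 46 is more than 80% power requires. It fits as an enrolled number with roughly 20% dropout (36.3/0.80 = 45.4, so 46), a rate the article does not state. The article also says "To compensate for dropouts, the study needs to enroll 46 participants per group for a total of at least 120 participants", which puts the surplus down to dropout. Both cases are therefore shown: 46 analysed, and 36 analysed (a loss of 10/46 = 22%).

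**Step 2: dilution model.** This is an assumption; the documents give no prior-use share. A share p of each arm already use the app and have no contrast, the effect in everyone else is 6 mmol/mol, and the SD stays at 9. Then:
- diluted difference = 6 × (1 − p)
- power = Φ(6(1 − p)/SE − 1.960), with SE = 1.877 for 46 per group and 9 × √(2/36) = 2.121 for 36 per group.

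| p | difference (mmol/mol) | power, 46 analysed | power, 36 analysed | n per group for 80% |
|---|---|---|---|---|
| 0 | 6.0 | 89.2% | 80.7% | 36 |
| 5% | 5.7 | 85.9% | 76.6% | 40 |
| 10% | 5.4 | 82.1% | 72.1% | 44 |
| 15% | 5.1 | 77.6% | 67.2% | 49 |
| 20% | 4.8 | 72.5% | 61.9% | 56 |

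**Step 3: where the margin runs out.** With 46 analysed, 80% power needs a difference of 1.877 × 2.802 = 5.26 mmol/mol, so p = 1 − 5.26/6 = about 12%. With 36 analysed there is almost no margin.

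**Step 4: partial loss.** If existing users lose half the contrast rather than all of it, the difference is 6 × (1 − p/2), so p = 20% gives the 10% row.

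**The case against.** **The intervention is more than the app.** This stands. An existing user allocated to the intervention would still receive SMASc scoring, a tailored plan, nurse interaction and the website, none of which the brochure group gets. A reader might infer that nothing new starts for such a person. The Trial Design, Intervention and Website sections contradict that, and zero contrast is therefore an upper bound.

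**No prior-use rate is known.** This also stands. A reader might infer that the contrast is already eroded at baseline, but the article gives no figure that shows it. With 46 per group analysed, power stays above 80% until about 12% prior use even under full loss of contrast.

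**Background app use may be part of usual care.** The objective is to add the intervention to usual diabetes care, so ordinary app use can reasonably belong to the comparator. This argues against excluding users of every diabetes app. It is weaker for the study app itself, which is the product being given to one arm.

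**An article may omit questionnaire detail.** That is fair: an app-use item could exist in the full protocol, so its absence here is not an error in itself. The eligibility criteria, however, are set out in the article, and they admit current users.

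**Workshop and interview participants.** A reader might extend the point to people who helped design the intervention. Of the workshop attendees, "6 were living with T2D, 2 were relatives of persons living with T2D". The article does not say that they received the app, that they are eligible or that they will enrol. If all six enrolled, split evenly and lost all contrast (6/92 = 6.5%), power with 46 analysed would be 84.8%. The number interviewed is not given. This does not justify a separate exclusion.

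**Conclusion.** The point holds as a possible dilution that the published criteria do not prevent and the listed assessments would not reveal. It is a matter of lost power and harder interpretation. It is not a bias between arms, because randomisation balances existing users on average.

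The size depends on an unknown prior-use share. With all 46 per group analysed, a 10% share costs at most about 7 percentage points of power (89.2% to 82.1%), and the planned 80% is still met. If dropout uses up the surplus, the same share takes power from 80.7% to 72.1%. These figures assume a two-sided 0.05 test, an SD of 9, a true difference of 6 mmol/mol in people new to the app, and complete loss of contrast in existing users, so the real loss at any given share should be smaller.

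**What to change.** - In Exclusion Criteria, add people who currently use the study app. Ask about it in the recruitment phone call that the research team already makes.
- Add one item on use of any diabetes app to the baseline, 4-month and 12-month questionnaires in all groups, so that background use and uptake among controls are known when the result is interpreted.
- Do not exclude users of other diabetes apps. Record that use instead, because excluding them would change the target population. No exclusion of workshop or interview participants is needed.

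The cost is one line in the criteria, one question in the call and one questionnaire item. The downside is a slightly smaller recruitment pool and a result that applies to people not already using this app.
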